#### Secondary outcomes—suggestions

A process analysis will examine how changes in outcomes may be explained by other factors. Controlling for demographic factors, mediation analyses will examine if changes in well-being and QoL are influenced by memory/recall of the art group, if improvements in social connections explain changes in QoL and well-being, and if recent arts engagement is associated with better outcomes.

The focus group data and open-ended questions from the questionnaire will be subject to thematic analysis^37^ This will explore the participants' views on what they liked and disliked, their feelings about the impact of taking part and social interactions. The self-report data will be integrated and analysed with the focus group and observation data, to enable a deeper understanding of the impact of the intervention.

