##### Data collection (people living with dementia)

The following quantitative and qualitative questionnaire data are collected in a face-to-face interview by the researcher at time 1 (baseline) prior to the start of the intervention, time 2 (follow-up) at the end of the intervention and time 3 (longer term follow-up) 3 months after the time 2 assessment.
Demographic data (eg, age, gender, marital status, socioeconomic status, education, residence).Social connectedness (Lubben Social Network Scale, six items;^31^ emotional and social loneliness, six items).^32^Dementia Quality of Life.^33^ A 28-item measure of QoL designed for people with dementia.Medication use (limited to particular types of psychotropics and those prescribed for dementia).Extent of engagement with art activities (qualitative).Expectations of taking part (qualitative, baseline only).Sense of belonging to community (five items).Memory of the sessions (qualitative, follow-up only).Perceived benefits and value (qualitative, follow-up only).

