##### Associated measures for people living with dementia

Clinical Dementia Rating Scale:^34^ administered at T1 only, to establish severity of the symptoms of dementia, completed by researcher.Dementia Quality of Life:^33^ a 31-item measure of QoL designed for carers of people with dementia (to be completed by carer or staff).Holden Communication Scale:^35^ assesses a range of social, behaviour and communication variables (to be completed through discussion with carer or staff member).

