#### Primary outcomes

Change over time (T1 and T2 and longer term T3) for significant improvements in the Dementia Quality of Life Scale (DEMQOL) and Holden Communication Scale will be ascertained using a repeated measures mixed-effects model. It will examine the extent to which the number of sessions attended, location, age, gender, education, socioeconomic status, medication use, Clinical Dementia Rating Scale (CDR) score and location are associated with outcomes. Differences between the three settings will be tested. Should these not be significant, data will be combined to increase sample size. Change over time in observed well-being between times 1 and 2, and differences between the control and intervention will be examined with a repeated measures mixed-effect model.

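### The mediation analyses are stated to control for demographic factors, which leaves out baseline dementia severity; recall or social connection can then falsely appear to explain change, and for QoL the result is an association only

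*Protocol article*

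**What the plan says.** Protocol article, Analysis of study sample 1, Secondary outcomes—suggestions: "Controlling for demographic factors, mediation analyses will examine if changes in well-being and QoL are influenced by memory/recall of the art group". The same sentence asks "if improvements in social connections explain changes in QoL and well-being". It names no other control and no exposure.

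Three other places bear on this:

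- **What demographic data are.** Data collection (people living with dementia) lists "Demographic data (eg, age, gender, marital status, socioeconomic status, education, residence". Severity is not among the examples.
- **Where severity is measured.** Associated measures for people living with dementia introduces the CDR separately, "administered at T1 only, to establish severity of the symptoms of dementia".
- **Where severity is used.** The Primary outcomes section for sample 1 asks how far factors including "medication use, Clinical Dementia Rating Scale (CDR) score and location are associated with outcomes". It also names the number of sessions attended.

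The recall item is listed as "Memory of the sessions (qualitative, follow-up only", so it has no baseline value. The QoL analysis is "Change over time (T1 and T2 and longer term T3) for significant improvements in the Dementia Quality of Life Scale (DEMQOL" and the Holden scale, with no group that goes without the programme.

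**The concern.** One proposed mediator is memory of the art sessions, in people who have dementia. Severity bears on that almost directly. It may also affect how QoL, well-being and social contact change over the following months. A common cause of mediator and outcome, left out of the model, produces a mediator-outcome association even when the mediator does nothing. Age, gender and education are weak substitutes for severity.

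The second difficulty is what the QoL result would mean. A mediated effect runs from exposure to mediator to outcome. Everyone contributing QoL data is offered the programme and no exposure is named for this analysis, so only the mediator-outcome link is estimated.

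The abstract asks how and why art makes a difference, the practitioners' manual is finalised after the data analysis, and the work is meant to inform a definitive trial. A mechanism that is really severity could pass into both.

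**Working it through.** **The plan's own figure.** The article gives no calculation for the mediation analyses. Its only sample size figure is N=80 for a 95% confidence level and 5% margin. Assuming a proportion of 0.5 and a finite population of 100 (neither is stated), it reproduces: n0 = 1.96² × 0.25 / 0.05² = 384.1; 384.1 / (1 + 383.1/100) = 79.5, rounded up to 80. It says nothing about mediation and is used here only as a plausible number analysed.

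**Inputs that must be assumed.** The article does not give the correlation of severity with the mediator (size a) or with change in the outcome (size b). The ranges taken are a = 0.3 to 0.7 and b = 0 to 0.5.

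**Formula.** Let standardised severity be S, mediator M = −aS + noise, outcome change Y = −bS + noise, with no effect of M on Y.

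- Without S in the model, the M–Y correlation is (−a)(−b) = ab: 0.3 × 0.3 = 0.09; 0.5 × 0.3 = 0.15; 0.5 × 0.5 = 0.25.
- With S in the model, the numerator of the partial correlation is ab − (−a)(−b) = 0, so the spurious path disappears.

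**Simulation.** There were 3,000 runs per scenario, with four demographic covariates unrelated to S and a two-sided 5% test on M. False-positive rate at n=80, demographics only:

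| a \\ b | 0 | 0.1 | 0.2 | 0.3 | 0.5 |
|---|---|---|---|---|---|
| 0.3 | 5% | 6% | 8% | 12% | 25% |
| 0.5 | 5% | 8% | 14% | 25% | 60% |
| 0.7 | 5% | 9% | 21% | 44% | 89% |

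With severity added, every cell lies between 4.1% and 6.0%. The Monte Carlo standard error at 5% is √(0.05 × 0.95 / 3000) = 0.4 percentage points.

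**Hand check.** By Fisher's z for a = 0.5, b = 0.3: atanh(0.15) × √77 = 0.151 × 8.775 = 1.33, and P(Z > 1.96 − 1.33) is about 26%, against 25% simulated.

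**Sensitivity.**

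- At n=100 the 0.3/0.3, 0.5/0.3 and 0.5/0.5 cells become 14%, 31% and 68%.
- If CDR measures severity with reliability 0.7 (a = 0.5, b = 0.3), adjustment takes the rate from 26% to 7%, so most of the bias goes.

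**Exposure, outcome by outcome.** QoL is analysed as change over T1 to T3 with no unexposed comparison. Observed well-being is different: Behavioural observation of people living with dementia sets up a within-person comparison of intervention and control conditions. Sessions attended could serve as a graded exposure. The secondary-outcomes text connects neither to the mediation analyses.

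**The case against.** The analyses sit under a heading that calls them suggestions, in an article that condenses a fuller plan. Naming demographic factors does not strictly exclude other controls, and the authors plainly know severity matters, since CDR is in the primary model. Residence is among the demographic examples, so setting may be partly covered; if residence or age tracks severity, some confounding is already absorbed and the rates above are too high. Recall is a qualitative item, whereas the simulation treats it as continuous. The how-and-why question also has other support: the realist synthesis, workshops, survey, focus groups and interviews.

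All of that limits the weight of the point, but it does not remove it. The article does state an adjustment set, and that set leaves out a measured variable that the same article uses one section earlier.

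Three stronger readings are tempting, and the documents do not support them:

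- **The study has no exposure contrast at all.** This is wrong for observed well-being, which has a concurrent within-person control condition; attendance also varies.
- **Severity is bound to produce a false mediator.** Bias needs severity to relate to change in the outcome, not only to its level. The article gives no figure for that, and if the correlation is zero there is no bias.
- **Social connection and QoL cannot be ordered in time.** The text does not specify a same-interval analysis. Both are measured at T1, T2 and T3, and the data-integration section mentions examining temporal aspects.

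**Conclusion.** The point holds in this form: the stated controls for the mediation analyses omit dementia severity, which is measured at T1 and used in the primary model, so recall or social connection can falsely appear to explain change. At n=80 the false-positive rate is about 5% if severity is unrelated to change, 6% at correlations 0.3/0.1, 12% at 0.3/0.3, 25% at 0.5/0.3 and 60% at 0.5/0.5. It is about 5% in all of these once severity is included. The correlations are assumptions, as are a continuous mediator and demographics unrelated to severity. The same arithmetic applies to social connection, with its own, possibly weaker, correlation with severity.

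For QoL, the analysis as described yields a mediator-outcome association, not a mediated effect of the programme. That limit does not extend automatically to observed well-being. The point concerns a secondary analysis and is cheap to correct, but it touches a headline question.

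**What to change.** In the secondary-outcomes section for sample 1, extend the stated controls to: demographic factors, T1 CDR, the T1 value of the outcome, setting, and number of sessions attended. Naming setting removes doubt about whether residence covers it. Report the QoL results as associations with change, not as mediated effects of the intervention.

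A lagged T2-to-T3 analysis of social connection and QoL is optional, as a sensitivity analysis.

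**Cost.** The change is wording; CDR and attendance already feed the primary model, so nothing new is collected. With linear terms for CDR, baseline outcome and sessions, and two indicators for three settings, the model spends 1 + 1 + 1 + 2 = 5 degrees of freedom. Adding severity also widens the standard error for the mediator by a factor of 1/√(1 − a²): about 15% at a = 0.5 and 40% at a = 0.7, before any gain from lower residual variance. The lagged analysis would lose participants missing at T3.

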##### Behavioural observation of people living with dementia

A within-participants/repeated measures 2×3 design will compare levels of well-being and engagement in two different conditions (intervention and control). The control condition is an unstructured activity. Using the Greater Cincinnati Chapter Well Being Observational Tool,^18^ observations are coded by the researcher according to the extent to which well-being and engagement are expressed at three time points: time 1, baseline (control condition only); time 2, at the start/within the first 2 weeks of intervention; time 3, the last 2 weeks of intervention. The Greater Cincinatti Chapter Well-Being Tool addresses seven domains of well-being—interest, sustained attention, pleasure, negative affect, sadness, self-esteem, and normalcy—and was developed specifically to observe the effects of visual arts on the well-being of people with dementia.

The aim of the observations in the control situations is to ensure a concurrent control for the person's function and interaction in the arts sessions, bearing in mind there may be changes over time unrelated to the project intervention. On that basis, we will undertake observations between situations within a few days of each other. Observations in each time point are carried out over 2 weeks to account for variability between sessions, as suggested by Brooker and Duce.^36^

This systematic method of observation enables an examination of the unconscious responses, that is, those that might not be verbalised during interviews. Where possible, the sessions are videoed to enable further analysis and validation. Care will be taken to ensure that others present who are not research participants cannot be identified in the filming. The videos are purely for research purposes and none of their content will be made public or shared beyond those involved in the analysis.

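### The planned mediation lacks time order for observed well-being and for T2 quality of life; only T3 DEMQOL follows a measured mediator

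*Protocol article*

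**What the plan says.** The relevant statements are all in the Protocol article.

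- **Planned analysis** (Analysis of study sample 1, Secondary outcomes—suggestions): "mediation analyses will examine if changes in well-being and QoL are influenced by memory/recall of the art group, if improvements in social connections explain changes". The outcomes meant are QoL and well-being. No lag or time order is given.
- **Interview times** (Data collection, people living with dementia): time 1 is before the start, then "time 2 (follow-up) at the end of the intervention and time 3 (longer term follow-up) 3 months after the time 2 assessment".
- **Mediators** (same section): "Social connectedness (Lubben Social Network Scale, six items", together with a six-item loneliness measure, at each interview; and "Memory of the sessions (qualitative, follow-up only".
- **QoL** (same section): DEMQOL, described as "A 28-item measure of QoL designed for people with dementia", is collected in those same interviews.
- **Observed well-being** (Behavioural observation of people living with dementia): time 1 is baseline; "time 2, at the start/within the first 2 weeks of intervention; time 3, the last 2 weeks of intervention".
- **Changes analysed** (Analysis of study sample 1, Primary outcomes): for QoL, "Change over time (T1 and T2 and longer term T3) for significant improvements in the Dementia Quality of Life Scale (DEMQOL"; for observation, "Change over time in observed well-being between times 1 and 2".

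**The concern.** Saying that a mediator explains a change in outcome implies that the mediator moved first. The schedule has two clocks with the same labels: time 2 is the end of the programme for interviews and the first fortnight for observations. Read together, they show that well-being is recorded early and late in the programme, while the mediators have no value after the start until it ends.

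Suppose people who take to the sessions early go on to make more contacts and to remember the sessions better. Their early gain in well-being would then correlate with later connectedness and recall. A mediation analysis could present those as the reason for the gain when the order was the reverse. This bears on the study's question of how and why art makes a difference. There is no randomised comparison to help separate the two directions.

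**Working it through.** The plan states no figure for this analysis, so there is none to reproduce. The check is a timeline.

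**Inputs.** The programme lasts 12 weeks (Self-reported outcomes from people living with dementia). The T2 interview is placed at about week 12. T3 is 3 months later, taken as 13 weeks, so 12 + 13 = week 25. The first observation fortnight after the start is weeks 0 to 2 in elapsed time, and the last is weeks 10 to 12.

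**First mediator value after the start.** Recall is asked at follow-up only, so its first value is at week 12. Connectedness has a baseline value, but its first value after the start, and so its first change score, is also at week 12.

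| Outcome after programme start | Elapsed weeks | First mediator value after start | Order |
|---|---|---|---|
| Observed well-being, time 2 | 0–2 | 12 | mediator 12 − 2 = 10 to 12 − 0 = 12 weeks later |
| Observed well-being, time 3 | 10–12 | 12 | mediator 12 − 12 = 0 to 12 − 10 = 2 weeks later |
| DEMQOL, T2 | 12 | 12 | same interview |
| DEMQOL, T3 | 25 | 12 | mediator 25 − 12 = 13 weeks earlier |

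One of the four outcome occasions follows a measured mediator. The stated well-being change uses the first row, where the order is plainly wrong. The self-report ratings after sessions do not help: they are collected in weeks 1–2 and 11–12, so they too are finished by the end of the programme.

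**Why simultaneous change scores cannot settle direction.** The test of a simple regression slope depends only on the correlation, and corr(ΔM, ΔY) = corr(ΔY, ΔM). An illustrative simulation shows this. It used n = 80 and 4000 runs per scenario. The assumptions, none from the protocol, were a standardised path of 0.4 between the changes and T3 QoL = 0.6 × T2 QoL + noise with SD 1, plus 0.3 × the T2 mediator in the forward scenario only.

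| Model | Mediator drives QoL | QoL drives mediator |
|---|---|---|
| T1–T2 QoL change on T1–T2 mediator change | significant in 96% | significant in 96% |
| T3 QoL on T2 mediator, given T2 QoL, T1 QoL and T1 mediator | significant in 66% | significant in 4% |

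The first model gives the same answer in both scenarios. The second separates them, with a rejection rate near the nominal 5% when the mediator has no effect. The 96% and 66% depend on the assumed sizes and do not predict this study. The equality in the first row does not depend on them.

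**The case against.** **The QoL mediation is not ruled out.** A reader might infer that the planned mediation can explain nothing. The documents do not support that. Primary outcomes names T3 among the QoL changes analysed, and both mediators are available three months earlier. A correctly ordered analysis is therefore within the plan. This stands and limits the point.

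**Date of measurement is not date of process.** T1–T2 change in connectedness covers the whole programme, and recall concerns sessions already held. For late-programme well-being and T2 DEMQOL the fair criticism is therefore that direction is ambiguous, not that explanation is impossible. The T2 interview may also fall within the last observation fortnight, so the mediator cannot be said to follow every observation strictly. Both stand. Neither rescues the change from baseline to weeks 1–2.

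**Lags and model form belong in an analysis plan, and these are headed as suggestions.** An article need not spell out a lagged model, and leaving it out is no fault. But the text does say that well-being will be analysed by mediation, and no analysis plan can create a mediator value before week 12. That part stands as a criticism of what the article fixes.

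**The study is exploratory.** It disclaims a robust test of effectiveness and also pursues how and why through interviews and focus groups. The data integration section recognises that the longitudinal data allow temporal questions. This lowers the severity, and it means the how-and-why question does not rest on this analysis alone.

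**A false-finding rate could be attached.** Assuming a correlation and n = 80 gives only the generic power to detect that correlation. It does not say how often this unspecified analysis would mislead, so no such rate is claimed.

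**Conclusion.** The point holds in three grades. For the stated well-being change, the mediators are first measured after the start about 10 to 12 weeks after the outcome, so a mediation claim is unsupported. For late-programme well-being they come 0 to 2 weeks after it, and for T2 DEMQOL at the same interview, so direction cannot be established. For T3 DEMQOL the order is right, by about 13 weeks.

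This rests on a 12-week programme, on the T2 interview taking place at about its end, and on times 1 and 2 in the well-being analysis being read on the observation clock. If the interview clock was meant there, the nearest observation is the last fortnight and the second grade applies.

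Severity is minor to moderate: the analysis is secondary and exploratory, but the unsupported wording can be avoided at almost no cost.

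**What to change.** In Secondary outcomes—suggestions for study sample 1:

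1. Report the relations of recall and connectedness to observed well-being, and to T1–T2 change in DEMQOL, as associations and not as mediation. The same paragraph already uses association wording for recent arts engagement.
2. Reserve any time-ordered mediation claim for T2 recall and T1–T2 change in connectedness as predictors of T3 DEMQOL, given DEMQOL at T1 and T2. State that conditioning on T2 makes this a question about QoL change after the programme ends, which is narrower than what explains gains during it.
3. Label the two clocks differently, for example Q1–Q3 for interviews and O1–O3 for observations, in the text and in the dataset.

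No new data are needed. The cost is fewer mediation claims and a lagged analysis that relies on retention to T3. Correct time order also does not by itself establish cause, since unmeasured common causes remain possible without a randomised comparison.

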### Study sample 2: staff and carers

#### Recruitment procedures

Across the three sites, the staff or carers are recruited as per the participants living with dementia. In sites 1 and 2, we will approach a wide range of professional care staff (eg, managerial, nursing, occupational therapists, care support workers, activity coordinators). In site 3, we will recruit participants who are the spouse, family member or friend of the participant with dementia. This involves three stages to gaining consent: (1) the researchers visit/promote and explain study; (2) potential participants express interest and receive information sheet, appointment booked to revisit (with sufficient cooling off period of 5 days); and (3) researchers meets with participant, explains study, answers questions, assesses capacity and obtains consent for participation.

##### Inclusion criteria

Member of staff in residential care homes or NHS facility, or spouse, family member or friend of the participant living with dementia.

##### Exclusion criteria

Recent or current episode of major mental illness.End of life/terminal illness.Inability to communicate verbally through the medium of either English or Welsh.

##### Data collection

The following quantitative and qualitative data are collected in a face-to-face interview with the carer or member of staff by the researcher at time 1 (baseline) prior to the start of the intervention, time 2 (follow-up) at the end of the intervention and time 3 (longer term follow-up) 3 months after the time 2 assessment.
Demographic data (eg, age, gender, marital status, post held).Self-reported health.Proximity to participant in relation to the intervention.Attitudes towards dementia—the Approaches to Dementia Questionnaire.^38^ A 19-item scale that assesses a person's attitudes to dementia, including subscales of ‘person-centred’ and ‘hope’.Perceptions of arts activities, and changes over time (single-item/open-ended questions).Changes in their friend/client/family member living with dementia (T3 only).

### Analysis of study sample 2

